### Recruitment {15}

Approximately 34 European and US centers will participate in this study (Fig. 1). All centers confirmed experience in machine Liver perfusion. The expected overall caseload in all centers is approximately 1400 Liver transplanted patients per year. Based on the expectation that one third of the transplanted population are HCC patients, i.e., 470 patients, and to recruit 50% of these cases, we estimate complete recruiting of 220 HCC Liver transplants within 1 year after the study start.

## Assignment of interventions: allocation

### Sequence generation {16a}

The computer-generated allocation sequence will be done in a 1:1 ratio using stratified block randomization with variable block sizes and stratification by study center. Stratification by center is important because there will be differences between centers with regard to the recipients of liver transplantation for HCC, due to different national or center-specific guidelines and criteria. Variable block sizes will better prevent surgeons from guessing the randomization sequence than fixed block sizes. Randomization lists will be created using the R package *blockrand* [32].

### Concealment mechanism {16b}

The centrally generated randomization lists (one per center) will be stored in the electronic data capture system SecuTrial® (interActive systems; iAs, Berlin). The lists will not be accessible by the study personnel who is screening and recruiting patients or entering data. The person who provided the randomization lists and the responsible data manager are the only persons with access to the randomization lists.

### Implementation {16c}

The R code to create the randomization lists will be prepared at the Department of Biostatistics of the Epidemiology, Biostatistics, and Prevention Institute, University of Zurich, Switzerland. An independent person at the Department of Clinical Research Basel, who is not otherwise involved in the trial, will then specify the random seed and run the code to produce the randomization lists. The random seed will determine the allocation and ensure reproducibility of the randomization lists. The randomization lists will then be handed over to the responsible data manager at the Department of Clinical Research, University Hospital Basel, Switzerland, who will store the lists in SecuTrial®. The allocation of a liver graft will be revealed to the transplant surgeon after the donor liver is accepted for transplantation to a particular recipient and is enrolled in the trial. More precisely, after inclusion and exclusion criteria are entered in SecuTrial®, the allocation will be done by clicking a “randomize” button in SecuTrial® by a designated member of the local study team.

## Assignment of interventions: blinding

### Who will be blinded {17a}

The allocation is blinded for all persons who perform the outcome assessments. Patients are also blinded. The statistician will be blinded for the sample size re-estimation during the interim analysis but will be unblinded for the final analysis. Surgeons are unblinded for the intervention as they are involved in the storage or perfusion process of the organs. However, the randomization result must not be listed on the surgery or any other report accessible to the study personnel not involved in the surgery to prevent unblinding.

### Procedure for unblinding if needed {17b}

If unblinding is required in the interest of a participant’s safety, the investigator will discuss the matter with the sponsor before unblinding. In a medical emergency, the principal investigator or delegate may unblind treating doctors via an “emergency unblinding” function in SecuTrial®, which requires password entry of the principal investigator or delegate and an additional confirmation for the unblinding. If the principal investigator is not available, the sponsor or a delegate from the project manager can be contacted at any time via phone for unblinding. When there is a breach of blinding, it will be recorded in the eCRF and the sponsor will be automatically notified. All unblinded cases will be included in the intention-to-treat analysis.

## Data collection and management

### Plans for assessment and collection of outcomes {18a}

Source data is sought from the following documents:Patient demographics and disease characteristics will be available in the clinic information systems.Donor information is routinely available to the transplant team during the organ allocation process from transplant coordinators and surgeons’ notes.Separate worksheets will be distributed for perfusion or cold storage details and (S)AE.Complications, blood results, and follow-up information will be collected from discharge notes and patient charts or nurse records as well as correspondence with other departments or family doctors. The blood samples for cDNA and HMGB-1 will be centrifuged within 2 h after sampling ad stored subsequently at −20 °C in the centers. The stored samples will be collected every 3 months and will be processed centrally at the University of Zurich.Histology and radiology reports will be collected for disease, graft information, and information about recurrence.

The sponsor is implementing and maintaining quality assurance and quality control systems with written SOPs and working instructions to ensure that trials are conducted, and data are generated, documented (record), and reported in compliance with the protocol, GCP, and applicable regulatory requirement(s).

A screening and enrollment log will be kept tracking the screening process and monitor the patient accrual and the progress of the study. Routine remote monitoring will regularly be conducted to check the completeness and plausibility of all data entered into the eCRF. Therefore, eCRFs will be kept current to reflect participant status at each phase during the study.

### Plans to promote participant retention and complete follow-up {18b}

Adherence to the intervention will be assured by training of the transplant surgeon if there is a deviation from the usual procedure at the respective center. After discharge, oncologic follow-up is according to recommended intervals and modalities and will be conducted by transplant surgeons, hepatologists, and oncologists.

### Data management {19}

The electronic data capture (EDC), GCP compliant software SecuTrial® will be used for data processing and management in the present project. SecuTrial® is provided and maintained by the Department of Clinical Research of the University Hospital Basel, Basel, Switzerland.

A current list with signatures and names of all authorized study personnel with access to the study data will be filed in the investigator site file and the trial master file, respectively. All the study files will be maintained by authorized study team members and are stored in a secured storage area. All data entry and correction activities as well as query resolution will be performed in each center by team members, who have the specific rights. SecuTrial® allows automatic data checks for completeness and plausibility. A built-in data logging tool (audit trail) ensures that any changes to the project or user activity (date and time stamp and user log) are continuously tracked in real time and accessible online or via downloadable audit table.

### Confidentiality {27}

SecuTrial® is an encrypted, online web tool and accessible only by secured log-in membership, to transfer the information from the source documents. It is assured that any authorized person, who may perform data entries and changes in the eCRF, can be identified.

In order to ensure patients’ confidentiality and compliance with data privacy regulations, a study-specific ID will be automatically generated for each patient, which allows pseudonymization of personal data. The List containing the Link between the patient pseudonym and the respective personal data will be stored appropriately by study coordinators and protected against unauthorized access. In case an audit or inspection is performed, all study data must be made available. The sponsor ensures that the study database will be securely stored until 20 years after the end of the study.

### Plans for collection, laboratory evaluation and storage of biological specimens for genetic or molecular analysis in this trial/future use {33}

All study data must be archived for a minimum of 20 years after study termination or premature termination of the clinical trial. All data will be stored on the server of the University Hospital Basel. The biological material (blood serum/plasma) will be stored at −80 °C for 5 years. Liver biopsies will be stored for 5 years.

## Statistical methods

### Statistical methods for analyzing primary and secondary outcomes {20a}

Detailed methodology for summaries and statistical analyses of the data collected in the trial will be documented in a separate statistical analysis plan. The statistical analysis plan will be finalized before database closure and will be under version control at the Department of Biostatistics, University of Zurich.

We will estimate the hazard ratio (HR) for the effect of HOPE versus conventional cold storage on the primary outcome and report the HR with a 95% confidence interval (CI) and a *p* value for the test of the null hypothesis of a HR of 1. To account for variability between centers, we will use a mixed-effects Cox model with treatment as a fixed factor and a random intercept per center, as implemented in the R package coxme, i.e., a frailty model with Gaussian frailty distribution [33]. The advantage of a mixed-effects Cox model over other approaches to account for between-center variability with time-to-event outcomes (e.g., center as fixed effect or stratification for center in standard Cox models) is that small numbers of patients and events per center are better handled [34]. It should be noted that the estimated HR will compare the hazard rates of two subjects, one treated with HOPE and one with conventional cold storage, randomly drawn from the same center (conditional HR, center-specific interpretation). We will assess the proportional hazards assumption by inspecting the scaled Schoenfeld residuals. HCC recurrence-free survival in the two trial arms will be graphically displayed by Kaplan–Meier curves. The analysis will be performed on the FAS (see item 20c). Patients who are lost to follow-up or withdraw from the trial will be right censored at their last follow-up visit.

As a sensitivity analysis for the primary outcome, we will estimate a HR that is further adjusted for prognostic factors for the primary outcome. The model described above will be fitted with additional baseline covariates, such as the score from the BAR (balance of risk) scoring system, vascular infiltration of the tumor, tumor grading, lymph node involvement, and downstaging treatment as additional covariates. However, we expect that the number of events will limit the number of variables that can be added to the model. We will therefore fit several covariate-adjusted models, each with a number of covariates that is appropriate. Further, to account for interval censoring of tumor recurrence (if observed at one visit, we only know it has occurred between this visit and the last visit), we will fit a mixed-effects Weibull survival model [35]. We will fit the model once ignoring the interval censoring (to assess the sensitivity of results to using this parametric model instead of a semiparametric Cox model) and once correctly accounting for interval censoring (to assess the sensitivity of results to accounting for interval censoring when using the parametric model).

Single components of the events considered for the primary outcome (tumor recurrence, HCC-related death, death from other causes) will be analyzed by cause-specific mixed-effects Cox models. We will account for competing risks by censoring patients with the competing event on the date of the competing event. We will use the Aalen-Johansen estimator to derive cumulative incidence function curves for all competing events. HMGB-1 on day 7 and circulating tumor DNA in blood at discharge and 6 months after transplantation will be analyzed by linear mixed-effects models, with corresponding measurements at baseline as covariates. The models will include a random intercept per center, and the one for circulating tumor DNA in blood will additionally contain a random intercept per patient, to account for the repeated outcome measurements. Log-transformation or a switch to a generalized linear mixed-effects model will be considered in case of violation of the normality assumption. Acute rejection index (ordinal outcome) will be compared between groups by a proportional odds model stratified by center [36]. The number of Liver-related complications experienced by the patient within 2 years will be analyzed the same way, since it is expected to be zero for a considerable proportion of the patients as in Schlegel et al. and thus analysis as a count is complicated [37]. As for the primary outcome, we will report effect sizes with 95% CI and *p* values for all secondary outcomes.

No statistical tests will be performed for other outcomes, but they will be descriptively compared between treatment arms.

### Interim analyses {21b}

When 165 patients are recruited (75% of 220 patients), a blinded sample size re-estimation will be performed. We will use the method proposed by Todd et al. for designs with flexible follow-up [38]. We will compare the average survival probability over both trial arms, S_new_(t), at t = 6, 12, 18, and 24 months of follow-up, from the data ad interim with the anticipated survival probability used for the original sample size estimation, S_orig_(t). The average difference (on the complementary log-log scale) will then be used to predict the overall tumor recurrence-free survival probability at 24 months, S_new_(24). We will re-estimate the required number of patients for the trial not only accounting for changes in survival probabilities but also for changes in the recruitment rate or in the dropout rate. The sample size will be increased if S_new_(t) > S_orig_(t) on average, i.e., if fewer events than expected are observed, given that the recruitment rate is as expected. A reduction of the sample size will not be considered. There are no statistical rules for stopping the trial earlier, neither for efficacy nor for futility.

### Methods for additional analyses (e.g., subgroup analyses) {20b}

Exploratory subgroup analyses are planned for the following baseline characteristics regarding the primary outcome: BAR score, vascular infiltration of the tumor, tumor grading, lymph node involvement, within/outside Milan criteria, tumor size, tumor nodule number, alpha-fetoprotein, downstaging treatment, and type of immunotherapy. For each subgroup variable, a mixed-effects Cox model will be fitted to the primary outcome. Treatment (HOPE vs. control), the subgroup variable, and the interaction between the subgroup variable and treatment will be included as fixed explanatory variables. A statistically significant interaction between one of the subgroup variables and treatment would indicate a different treatment effect in the corresponding subgroups or along the continuous baseline characteristic. For categorical subgroup variables, group-specific treatment effects (with 95% CI) will be computed, fitting a separate model for the corresponding subgroups, which will be reported together with the interaction *p* value. Since these subgroup analyses are exploratory, we do not plan to adjust *p* values for multiple testing.

To investigate associations of characteristics of the liver explant (e.g., tumor staging and grading, phenotype of tumor infiltrating and tumor stroma immune cells) and characteristics of the implant directly after transplantation (T cells and monocytes) with the primary outcome, descriptive tables will be created of these parameters in terms of the primary endpoint.

To assess the heterogeneity of the treatment effect among centers, Higgin’s *I*^2^ will be estimated [39]. To assess whether the effect of HOPE vs. conventional cold storage differs from that of DHOPE vs. conventional cold storage, the intervention group will be split into HOPE and dual HOPE, and the model described above for the primary outcome will be fitted with this three-level factor for treatment.

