### Intervention description {11a}

All study centers will use either a VitaSmart®, Liver Assist®, or Perlife® device for machine liver perfusion (Fig. 3), with a pressure-controlled hypothermic oxygenated liver perfusion through the portal vein (HOPE) or through the portal vein and the hepatic artery (DHOPE). The rationale to choose VitaSmart® and Liver Assist® is based on their CE sign and the clinical experience during recent and ongoing RCTs [18–20] (NCT05045794). Perlife® also has a CE sign and is used currently in another RCT (NCT04644744). There are no RCTs comparing the effectivity of HOPE vs. DHOPE. However, recent cohort and experimental data show no differences between HOPE and DHOPE in terms of perfusion quality and also in terms of outcome [18, 21–23]. The oxygenation process of the perfusate is similar, as the same oxygenators are used. The perfusion flow in both procedures is pressure controlled. For the sake of simplicity, we therefore refer to HOPE/DHOPE as HOPE throughout the manuscript. The targeting pressure is 3–5 mmHg and the perfusate temperature is between 8 and 12 °C. The perfusate consists of 3L recirculating Belzer MPS® (Bridge to Life Ltd.) with active oxygenation (70–110 kPa). The minimum perfusion duration is defined as 2 h, while perfusion is generally continued until the recipient hepatectomy is completed, i.e., if the recipient hepatectomy takes longer, perfusion is extended. The absolute upper Limit for HOPE is 24 h according to recent publications [24, 25]. The perfusion device is routinely used in all participating centers. All machines used are certified for human use and controlled by transplant surgeons. Cooling of the perfusate is managed by a heat exchanger (Liver assist®) or ice (VitaSmart®); the perfusion flow is adjusted to 150–250 ml/min under pressure control (< 5 mm Hg). Commercially available, CE-certified and approved Belzer MPS solution will be used (Belzer MPS-UW-Machine perfusion solution, Bridge to Life®) as perfusate for machine perfusion (according to clinical routine).

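### The HOPE versus DHOPE comparison splits only the intervention arm against pooled controls, so any baseline-risk difference tied to technique enters the contrast

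*Protocol article*

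**What the plan says.** The comparison is described at the end of the protocol article's section on additional analyses {20b}. Its purpose is "To assess whether the effect of HOPE vs. conventional cold storage differs from that of DHOPE vs. conventional cold storage". To do this, "the intervention group will be split into HOPE and dual HOPE". On how the split is then analysed, the section states that "the model described above for the primary outcome will be fitted with this three-level factor for treatment". Controls from all centres form the third level.

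The primary model it borrows is in section {20a}: "we will use a mixed-effects Cox model with treatment as a fixed factor and a random intercept per center". The random intercept is the only adjustment for centre.

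The Intervention description {11a} permits either technique, gives no rule for choosing between them, and notes: "There are no RCTs comparing the effectivity of HOPE vs. DHOPE". It goes on to cite cohort and experimental data showing no difference in perfusion quality or outcome, and treats the two as one intervention on that basis. Sequence generation {16a} randomises perfusion against cold storage by "stratified block randomization with variable block sizes and stratification by study center"; technique plays no part in it. The same section explains: "Stratification by center is important because there will be differences between centers with regard to the recipients of liver transplantation for HCC".

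For every other subgroup variable, section {20b} specifies treatment, the subgroup variable and their interaction as fixed effects.

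**The concern.** The question is one of effect modification: is the benefit over cold storage the same for both techniques? Answering it requires each technique to be compared with controls who share its baseline risk. In the three-level factor the controls carry no technique label. The common control level drops out of the contrast of the two HRs, leaving DHOPE recipients against HOPE recipients, a comparison that was not randomised. Controls can help only indirectly, through the centre intercepts, and with fewer than one event per centre on average those intercepts are heavily shrunk.

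At stake is the check on pooling HOPE and DHOPE as one intervention. If risk happens to line up with technique, the analysis could show a difference between techniques that have the same effect.

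**Working it through.** **1. The plan's own figure.** Inputs from Sample size {14}: 24-month risks of 15% and 5%, 12 months' accrual, 36 months in total, 80% power, 5% level.

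- Monthly hazards: −ln(0.85)/24 = 0.00677 and −ln(0.95)/24 = 0.00214, so HR = 0.316 (stated as 0.32).
- Event probability, p = 1 − (e^(−24λ) − e^(−36λ))/(12λ): 0.1836 (control) and 0.0621 (HOPE); at the mean hazard 0.00445, p̄ = 0.125.
- N = [1.96·√(4/p̄) + 0.84·√(2/0.1836 + 2/0.0621)]² / (ln 0.316)² = 207.5, so 208.
- Events = 207.5 × (0.1836 + 0.0621)/2 = 25.5, so 26. Then 208/0.95 = 219, against the stated 220.

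The plan's numbers are reproduced with a two-sided test. The protocol gives no figure for HOPE against DHOPE.

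**2. Information available.** Expected events are 104 × 0.0621 = 6.5 in the whole HOPE arm and 104 × 0.1836 = 19.1 in controls. Over about 34 centres, 26/34 = 0.76 events per centre.

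**3. What the three-level factor estimates.** Let the true log hazard be δ × (DHOPE centre) + θ × (perfused), with the same θ for both techniques. The correct contrast is 0. The fitted model has no technique term for controls, so only the centre intercepts can absorb δ. Whatever shrinkage leaves behind appears as a DHOPE–HOPE difference.

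**4. Size, by simulation.** Set-up: 220 patients in 34 centres, 1:1 within centre, identical true effect of both techniques. Assumptions not in the protocol: technique fixed by centre, 17 centres each; residual between-centre SD 0.3; baseline hazard ratio of DHOPE to HOPE centres as listed. The fitted model was a constant-hazard Gaussian frailty model, standing in for the mixed-effects Cox model, with a likelihood-ratio test at 5% and 600 runs per setting.

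| Baseline ratio (assumed) | Median DHOPE/HOPE ratio, HR 0.32 | False positives | Median ratio, HR 1 | False positives |
|---|---|---|---|---|
| 1 | 0.96 | 3.5% | 0.97 | 6.0% |
| 1.5 | 1.37 | 5.0% | 1.40 | 11.5% |
| 2 | 1.77 | 8.8% | 1.86 | 22.0% |
| 3 | 2.43 | 19.0% | 2.60 | 45.5% |

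The true ratio is 1.00 throughout. Simulation error in the rates is about 1 to 2 percentage points. Dropout was not simulated, so events at HR 0.32 run at 28 to 31 rather than 26.

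A second simulation (Cox model with Gaussian frailty, 208 patients, two-fold baseline ratio only, runs with an empty event cell dropped) gave ratios of 1.73, 1.90 and 1.93 at HR 0.32, 0.60 and 1, with false-positive rates of 3%, 12% and 24%.

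**5. What the random intercept removes.** At a two-fold baseline ratio: 1 − ln 1.77/ln 2 = 18% (HR 0.32) and 1 − ln 1.86/ln 2 = 10% (HR 1). Across the settings it is about 10% to 20% of the baseline log-ratio. Even with ten times the patients at HR 0.32, spurious ratios of 1.27, 1.40 and 1.40 remain for baseline ratios of 1.5, 2 and 3.

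**6. The alternative model.** With treatment, technique and their interaction, the first simulation gives median ratios of 0.94 to 1.00 (HR 0.32) and 0.99 to 1.02 (HR 1), with false-positive rates of 4.3% to 6.2% at every baseline ratio. The second gives 0.90 to 1.03 and 3% to 4%.

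**7. Precision.** With an equal split (assumed), there are 3.23 events per technique in the HOPE arm and 9.55 in the matching controls.

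- Three-level contrast: SE = √(2/3.23) = 0.79; 95% CI a factor of e^(1.96×0.79) ≈ 4.7 either way.
- Interaction: SE ≈ √(2/3.23 + 2/9.55) = 0.91; a factor of about 6.0 either way.

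**The case against.** The strongest reply is that the mechanism depends on facts the protocol does not state.

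- **Technique by centre.** A reader might infer from centre-level devices and routine that each centre uses one technique. The protocol does not say so, and its schedule lists perfusion type per patient. If operators choose within a centre, the simulation does not apply. This stands, and makes the size conditional. It does not rescue the analysis: the split would still be unrandomised, with possible confounding by graft or patient, which a centre intercept cannot address.
- **Alignment of risk.** A reader might take the expected differences in recipients between centres as an expected difference between HOPE and DHOPE centres. The protocol says only the former. Without systematic alignment there is essentially no bias (first row of the table). Chance imbalance alone is small: 0.3 × √(2/17) = 0.10 on the log scale, a ratio of about 1.11, so a two-fold difference would have to be systematic. This stands, and is why a range starting at 1 is shown.
- **Error rate at the design effect.** At HR 0.32 and a two-fold ratio the two simulations give 3% and 9%, a modest or absent excess. This stands. They differ in model, in test and in handling of empty event cells, and the number of dropped runs is unknown, so a range is the fair statement. The section also names no formal test or threshold for this contrast.
- **Hiding a real difference.** A reader might expect the bias to mask one as well. Every setting simulated had identical true effects, so no size can be put on that.
- **Consequence.** This is an additional analysis, too imprecise under either model to settle the question. That lowers the priority. It does not justify a model that leaves out the term the same section includes for its other subgroup variables.

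**Conclusion.** The point holds in conditional form. The three-level factor does not isolate a difference in treatment effect between techniques. It mixes that difference with whatever baseline-risk difference accompanies an unrandomised choice, and at about 26 events in 34 centres the random intercept does little to separate them.

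If technique is set by centre and baseline hazards differ 1.5- to 3-fold, the spurious ratio is about 1.4 to 2.4 at HR 0.32 and 1.4 to 2.6 at HR 1. Any excess of false positives at HR 0.32 is small up to a two-fold difference, so the main harm there is a misleading point estimate. If perfusion has no effect, the false-positive rate reaches about 12%, 22–24% and 46% at baseline ratios of 1.5, 2 and 3.

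The documents do not support saying that this bias will occur, or that the primary result is compromised: the primary model does not use the split. This is a cheap, low-priority improvement.

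**What to change.** Classify each centre by the technique it uses, fixed before recruitment. At centres using both, record the intended technique for each patient before randomisation. Apply the label to controls as well as perfused patients.

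Replace the three-level factor with treatment, technique and treatment-by-technique, keeping the random intercept per centre. Report the interaction with its 95% CI as exploratory, and state that technique was not randomised.

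The cost is one extra data field, a pre-randomisation entry at mixed centres, and an interval wider by the margin shown in step 7 of the working. With about 6.5 events expected in the whole HOPE arm, that width reflects what the trial can say about technique. The interaction model removes a baseline difference shared by treated and control patients; it does not make the choice of technique random.
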